### Motor ISA-Assessment

A common method to evaluate self-awareness is by comparing self and outside assessments. In this study we use the recently developed and validated measurement method by Maier et al. (2015). The patient is shown several video clips where a healthy person demonstrates various movements. The task for the patient is to repeat the movement him/herself as seen in the video clip. The following 15 symptoms are examined:

1.Sitting on a chair: resting tremor (left and right hand), dyskinesia.2.Right hand pronation-supination: speed and amplitude of movement, dyskinesia.3.Left hand pronation-supination: speed and amplitude of movement, dyskinesia.4.Arising from a chair: resting tremor (left and right hand), dyskinesia.5.Walking down an aisle: resting tremor (left and right hand), dyskinesia.

The symptoms are distributed across the four subscales dyskinesia, resting tremor right hand, resting tremor left hand and bradykinesia. Following each task, the patient rates his/her performance on a dichotomous scale whether the movement was impaired or not. Regarding the perception of a symptom, in total each patient answers 15 questions with either yes or no. The whole procedure is recorded by video. Later, independent raters evaluate the movements as well. In case of any discrepancies – if the patient does not see any impairment, although the raters do – an impaired self-awareness is noted. For each symptom, irrespective of the patient’s awareness, they also rate its severity according to UPDRS-III (values range 0–4; 0 = normal/absent; 1 = mild; 2 = moderate; 3 = severe; 4 = unable to perform). This procedure allows the calculation of two independent scores: one score for overall motor impairment severity and a second score for ISAm severity. While the motor impairment score is calculated by summing up all motor severity ratings, the ISAm score is calculated by summing up all motor severity ratings of the potential 15 discrepancies. Hence, both scores can vary between 0–60. In the medication ON-state the ISAm global score can also be divided into subscores for impaired self-awareness for hypokinetic symptoms (ISAm-Hypo for tremor and bradykinesia) and hyperkinetic symptoms (ISAm-LID).

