### Planned Statistical Analyses

The results of a power analysis suggest, that a total of up to 166 patients (83 patients per group) might be needed to detect a significant effect. By applying a group sequential study design the number of patients needed is raised to 180 to allow for interim analyses to be performed after including 60 and 120 patients, respectively. To the best of our knowledge the motor ISA-Assessment has not been applied in a longitudinal study design. Depending on the results of these interim analyses or due to economic reasons, the study might be stopped beforehand.

Demographic and baseline characteristics will be compared using *t* tests or other non-parametric methods, if necessary. To analyze most of the primary and secondary outcomes, performing repeated-measures mixed model analyses of covariance will be essential. Independent variables will be group (intervention and waitlist) and time (pre, post and 8-week follow-up) and also their interaction. Baseline measure, the amount of medication (levodopa equivalent daily dose) and depression scores will be included as covariates. To specifically analyze ISAm scores, which are the main outcome, and to determine their degree of objectiveness, inter-rater reliability will be computed for each measurement point in time.

In order to get more insight into possible mechanisms of mindfulness, ISA and their connection to each other, several moderation and mediation analyses are planned. For example, we expect the number of completed training sessions, motor symptom severity and patients’ general cognitive performance level to be possible moderating factors affecting mindfulness scores itself and/or the relationship between mindfulness and ISA. Among others, mediating factors considered will be cognitive performance of sustained attention and questionnaire scores of negative emotions like anxiety and depression. Of course, neurobiological changes will be included as well.

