### Strengths of This Study

This study is conducted with the expectation of further insight into the phenomenon of impaired self-awareness in PD and its relation to practiced mindfulness. Therefore, in the following the study’s strengths are highlighted.

For once, this is the first project to study the relationship between self-awareness and mindfulness in PD which also collects longitudinal quantitative and qualitative behavioral and neurobiological data. Though the planned sample size of up to 180 patients is quite large, it has to be noted that the study might be stopped beforehand due to economic reasons or a lack of eligible patients. However, sample sizes of other studies were much smaller (usually around 10 to 15 patients with one study including around 60 patients). Despite a small sample size, they also found significant effects for mindfulness related aspects (Advocat et al., 2013; Pickut et al., 2013; Cash et al., 2016; Dissanayaka et al., 2016; Birtwell et al., 2017). Additionally, similar to other studies the interventional effect is compared to a waitlist-control group but not an active control group. The planned training duration of 8 weeks are standard and, based on described literature, should be adequate to achieve significant changes. If a significant impact is found in this sample, an active control group and longer time intervals between measurements should be considered for further evaluation of the training protocol.

A main part of this study is the evaluation of ISAm, which is done by using a psychometric evaluated tool developed by Maier et al. (2015). This method is similar to the evaluation of ISAm in previous studies (Maier et al., 2016). In our study, however, it is for the first time assessed with repeated measurements. Also, we only assess ISAm during the medication ON-state, but not in the OFF-state. Not taking their medication would be another heavy strain for each patient, and we therefore decided to refrain from OFF-state evaluation of ISAm. Additionally, the ON-state is more accurate in reflecting the patient’s daily life situation. As we also focus on the implications of mindfulness in everyday life during an interview, we get the opportunity to combine qualitative and quantitative data. Future studies might also focus on the evaluation of OFF-state ISAm. As this is also the first time this method is used in a longitudinal study, its sensitivity to change is still unknown.

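### Inter-rater reliability of the ISAm score would share the patient's own answers across raters, so it cannot by itself show that the ratings are objective; report agreement on the 15 raw ratings beside it

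*Protocol article*

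**What the plan says.** The Planned Statistical Analyses section takes the ISAm scores, the main outcome, as the target of the reliability check and gives its purpose: "to determine their degree of objectiveness, inter-rater reliability will be computed for each measurement point in time". It names no coefficient, no number of raters and no unit of analysis.

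The Motor ISA-Assessment section defines the score:

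- The patient's part: "in total each patient answers 15 questions with either yes or no".
- The raters' part: "Later, independent raters evaluate the movements as well", working from video. They grade every symptom for severity whether or not the patient noticed it ("values range 0–4; 0 = normal/absent; 1 = mild; 2 = moderate; 3 = severe; 4 = unable to perform").
- A discrepancy is recorded "if the patient does not see any impairment, although the raters do".
- The total: "the ISAm score is calculated by summing up all motor severity ratings of the potential 15 discrepancies".

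The same section also defines a motor impairment score, the sum of all severity ratings, which does not use the patient's answers.

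On change over time, the Strengths of This Study section says: "As this is also the first time this method is used in a longitudinal study, its sensitivity to change is still unknown".

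**The concern.** The ISAm score has two ingredients. The raters supply severity; the patient supplies a mask that sets every admitted item to zero. The mask is the same whichever rater is scored, so two raters' ISAm scores for one patient move together simply because that patient denied many items or few. A reliability coefficient on the score credits this shared movement to the raters, although it comes from the patient's self-report.

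The stated purpose is to learn how objective the scores are. A coefficient that can be clearly positive with no rater agreement is weak evidence for that, and the trial could report more reassurance about its primary measure than the ratings support. A coefficient between raters at a single visit is also silent on the reliability of change, which is what the primary outcome uses.

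**Working it through.** **Plan's own figure.** 5 tasks × 3 symptoms = 15 items; 15 × 4 = 60. This matches the stated score range of 0–60. The article gives no reliability value to reproduce.

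**Model.** For rater r, ISAm_r = Σ D_i × S_ri over the 15 items. D_i = 1 if the patient denies item i (shared by all raters), and S_ri is rater r's severity, 0–4. Let K = ΣD_i, the number of denied items.

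**Assumptions not in the documents:** two raters; an ICC; each rater's own ISAm sum is formed; severity has mean m and variance v and is unrelated to D; K is beta-binomial with denial share p and within-patient correlation ρ.

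**Chance-only raters** (severities independent between raters and items):

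- Covariance between raters = m² Var(K)
- Variance per rater = m² Var(K) + v E(K)
- ICC = Var(K) / [Var(K) + cv² E(K)], with cv² = v/m²
- E(K) = 15p and Var(K) = 15p(1−p)(1 + 14ρ)

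**Worked example.** Severity probabilities for grades 0–4 of 0.4, 0.3, 0.2, 0.1, 0 give m = 1, v = 1, cv² = 1. With p = 0.5, E(K) = 7.5.

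| Denial probability | ρ | Var(K) | SD(K) | ICC of ISAm |
|---|---|---|---|---|
| Beta(1,1) | 1/3 | 3.75 × 5.667 = 21.25 | 4.6 | 21.25/28.75 = 0.74 |
| Beta(2,2) | 1/5 | 3.75 × 3.8 = 14.25 | 3.8 | 14.25/21.75 = 0.66 |
| Beta(4,4) | 1/9 | 3.75 × 2.556 = 9.58 | 3.1 | 9.58/17.08 = 0.56 |

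Simulation of these three settings gave 0.737, 0.660 and 0.562. The motor sum over all 15 items gave about 0.00 for the same raters.

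**Other inputs:**

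- No extra spread in denial (ρ = 0, p = 0.5, cv² = 1): 3.75/11.25 = 0.33. With cv² = 1.5: 3.75/15 = 0.25.
- Mostly absent or mild symptoms (cv² = 2.75, p = 0.5, ρ 0.2 to 0.33): 0.41 to 0.51.
- Lowest of the grid (cv² = 4.6, p = 0.7, ρ = 0): 3.15/(3.15 + 48.3) = 0.06.
- Highest (cv² = 0.5, p = 0.3, ρ = 0.5): 25.2/(25.2 + 2.25) = 0.92.
- Entry requires some evidence of ISAm on a screening tool. As a rough stand-in, keeping only patients with one rater's ISAm above 0 lowers the Beta(1,1) example from 0.74 to 0.68.

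**Discrepancy kappa.** Scoring each item as discrepancy yes/no does not avoid the problem. With q = P(severity > 0), chance-only raters give kappa = q(1−p)/(1−pq). For q = 0.6 and p = 0.5 this is 0.3/0.7 = 0.43. The simulated range was 0.08 to 0.67.

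**Raters who do agree.** Split unit severity variance into a patient part t, a patient-by-item part u and rater error e. Then:

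- Item ICC = t + u
- Motor-sum ICC = (15t + u)/(15t + u + e)
- ISAm ICC = C/(C + e E(K)), with C = Var(K) + t E(K²) + u E(K)

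Under Beta(4,4), E(K²) = 9.58 + 56.25 = 65.83. Solving t and u from the item and motor ICCs of a simulation:

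| Item ICC | Motor ICC | t, u, e | C/(C + 7.5e) | Simulated ISAm ICC |
|---|---|---|---|---|
| 0.18 | 0.49 | 0.043, 0.137, 0.82 | 13.47/19.62 = 0.69 | 0.69 |
| 0.33 | 0.68 | 0.078, 0.252, 0.67 | 16.62/21.64 = 0.77 | 0.77 |
| 0.55 | 0.83 | 0.118, 0.432, 0.45 | 20.57/23.94 = 0.86 | 0.87 |

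The gap between the ISAm and motor coefficients shrinks from 0.20 to 0.09 to 0.04 as true agreement rises.

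**The case against.** The strongest reply is that the premise is not written down. The article never says that a separate ISAm sum is formed for each rater. Its plural wording on discrepancies would also fit a pooled or consensus rating. The planned sentence is compatible with computing agreement on the raw ratings, and the choice of coefficient and unit is normally left to a fuller document. This stands: the point is conditional on the coefficient being computed on ISAm scores or discrepancies.

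A score-level coefficient is also not wrong in itself. Denial of visible symptoms is part of the construct, and how far the analysed score would move if the rater were swapped is a fair question. This stands too, and is why that coefficient should be kept. It answers a different question from whether raters agree on what they see.

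Zero agreement is, moreover, an extreme case for raters scoring video on an anchored scale.

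Three stronger readings are tempting and unsupported:

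- **That the trial's coefficient would be inflated to 0.56–0.74.** Every input behind that interval is assumed.
- **That the treatment comparison is compromised.** No eligibility rule, stopping rule or test is stated to depend on this coefficient.
- **That the authors overlooked reliability of change.** They disclose that sensitivity to change is unknown and add a semi-structured interview for that reason. Nothing in the article presents per-visit rater agreement as evidence about change.

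**Conclusion.** The point holds in a limited form. If inter-rater reliability is computed on ISAm scores or discrepancies, it mixes rater agreement with between-patient differences in denial and is positive for chance-only raters whenever patients differ in how many items they deny. It cannot alone establish objectivity.

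The documents do not determine the size. The grid of about 0.06 to 0.92 covers cv² 0.5–4.6, p 0.3–0.7 and ρ 0–0.5, with two raters and an ICC assumed. At item ICC 0.55 the inflation is about 0.04. The mechanism is certain given the score definition; its practical weight depends on how well the raters actually agree. This is an inexpensive improvement to a supporting analysis.

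**What to change.** State that, at each visit, inter-rater agreement will be computed on the raters' own ratings of all 15 items regardless of the patient's answers: kappa for presence or absence, and weighted kappa or ICC for severity and for the motor impairment sum. Report the ISAm-score coefficient beside these, labelled as showing how far the score depends on the rater. Name the coefficient and the number of raters.

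Optionally, use the waitlist arm's pre and post scores to report a test-retest ICC and the standard error of measurement for ISAm. That arm is measured at the same intervals without the intervention, so this gives some evidence on the noise in change scores.

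The cost is a few extra analyses on ratings already collected, with no new data or patient burden. The downside is a possibly less favourable reliability figure.

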### Outcome Measures

The main goal of this study is to increase self-awareness for motor symptoms. Therefore, the primary outcome for efficacy testing is a global ISAm-score. To be precise, mainly its change from baseline to post-intervention assessment is analyzed to evaluate the effectiveness of IPSUM. Changes of ISAm from baseline to follow-up are considered as a secondary outcome. However, we determined several other secondary outcomes like general neuropsychological test performance, the congruence between neuropsychological test performance and subjective daily life impairment (ISAc) and the congruence between objective neuropsychological test performance and subjective test performance (metacognition). Also, changes of several PD related symptoms (depression, apathy, impulsivity, sleeping problems) and affective states (stress, anxiety, quality of life, mindfulness) are analyzed. The aforementioned secondary outcomes comprise all changes from baseline to post measurement as well as changes from baseline to follow-up measurement. Additionally, structural neurobiological changes in the Insula and Cingulate Cortices, as well as any kind of reported subjective changes during the semi-structured interview are also considered when IPSUM’s effectiveness is evaluated.

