When the effectiveness of a treatment is evaluated, the question of how to deal with dropout patients has to be considered. If a patient cannot conclude his or her study participation, the reason and time of drop out will be documented. To still be able to include as many patients as possible in the analyses, the intention-to-treat analysis is preferred. For missing values, missing at random-analyses will be performed. In case of positive results, maximum likelihood methods will be applied. Data will be analyzed using SPSS, version 26.0 (IBM Corp., Armonk, NY, United States). To analyze qualitative data collected during semi-structured interviews, qualitative content analysis will be used (Mayring, 2015).

Imaging fMRI data will be analyzed using SPM12 (Penny et al., 2007). Functional connectivity of the left and right anterior insula and the anterior cingulate – central nodes of the salience network which have repeatedly been described to be altered following mindfulness interventions – will be analyzed by comparing pre to post measurements within and between groups, focusing on connectivity with the medial prefrontal cortex and the default mode network (Kilpatrick et al., 2011; Doll et al., 2015). Voxel-based morphometry will be applied to perform pre-post between-group comparisons of gray matter density in the same regions. Diffusion MRI will be used to analyze training effects on fractional anisotropy of the anterior-superior parts of the corona radiata and corpus callosum, following results reported after a similar intervention in healthy subjects (Tang et al., 2010). Neural correlates of impaired self-awareness (motor and cognitive) will be assessed based on previous findings in FDG-PET, with the cingulate gyrus and right insular cortex as regions of interest in morphometric and functional connectivity analyses.

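### Maximum likelihood is made conditional on a positive missing-at-random analysis, a condition that observed data cannot verify

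*Protocol article*

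**What the plan says.** All the text on missing data stands in one paragraph of Planned Statistical Analyses in the Protocol article. For patients who leave, "the reason and time of drop out will be documented". On the analysis set, it says "To still be able to include as many patients as possible in the analyses, the intention-to-treat analysis is preferred". It then sets out two steps: "For missing values, missing at random-analyses will be performed. In case of positive results, maximum likelihood methods will be applied". No procedure is named for the first step, a positive result is not defined, and no method is given for any other result.

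Earlier in the same section the main model is fixed without reference to missingness: "To analyze most of the primary and secondary outcomes, performing repeated-measures mixed model analyses of covariance will be essential". Under Outcome Measures, the primary outcome is the global ISAm score, and "mainly its change from baseline to post-intervention assessment is analyzed to evaluate the effectiveness of IPSUM". A missing post-intervention visit therefore removes the primary endpoint for that patient.

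**The concern.** MAR is a statement about how missingness relates to the values that were not seen, given those that were. It is an assumption to be argued from the design and the reasons for dropout, and the observed data cannot deliver a verdict on it. A plan that waits for such a verdict before using likelihood methods can go wrong in two ways. A positive result gives reassurance that is not warranted. A negative result may set aside a method that is valid. In both cases the choice of method is made after the data are in.

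The setting makes this more than a formality. Only the intervention arm attends eight weekly sessions of about 2 hours, with home practice rising to 30 minutes a day, while controls are treated as usual. Dropout that differs between the arms and depends on engagement is plausible, although the article gives no expected rate.

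**Working it through.** The plan gives no figure on this point to reproduce, so the check has two parts: a comparison of the statements, and a simulation of what a check on observed data can show.

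**Statements side by side.** The mixed model is named for most primary and secondary outcomes with no condition. The missing-data rule allows maximum likelihood only after a positive result. If the mixed model is fitted by likelihood, it already uses every available visit under MAR, and the condition has no proper place. If a classical repeated-measures analysis of covariance is meant, it needs complete records, and the condition decides whether incomplete records are used. The article does not say which is meant.

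**Simulation inputs (all assumed).** 90 patients per arm; 4,000 runs per scenario; baseline Y0 standard normal; post score Y1 = 0.6 × Y0 + 0.8 × e, with e standard normal. The variance of Y1 is 0.36 + 0.64 = 1, so results are in SD units, and the baseline-post correlation is 0.6. The check is a t-test at the 5% level comparing the baselines of patients with and without a post score. The estimate is the baseline-adjusted group difference in patients with a post score.

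**Part A: can the check tell MAR from MNAR?** Post scores are missing for 25% of the intervention arm and 10% of the control arm. The unseen scores of intervention dropouts are shifted by δ. The group difference in the full data should be 0.25 × δ, that is 0, 0.125 and 0.25. The observed data follow the same distribution in all three cases.

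| δ (SD) | Check rejects | Estimate from observed data | Difference in full data |
|---|---|---|---|
| 0 | 5.4% | 0.001 | 0.001 |
| 0.5 | 4.5% | -0.001 | 0.124 |
| 1.0 | 5.4% | 0.003 | 0.253 |

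The check rejects at about its nominal 5% throughout, while the error in the estimate grows from 0 to 0.25 SD. A passed check says nothing about whether MAR holds.

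**Part B: what if the check is really one of MCAR?** Here the log-odds of a missing post score are -1.8 + 1.0 × Y0 in both arms, so MAR holds given baseline. The check rejects in 99.75% of runs, yet the baseline-adjusted estimate averages -0.001 against a true value of 0. A rule requiring the check to pass would withhold likelihood methods in almost every run, although they are valid here.

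**Limit of the simulation.** With one post visit and complete baselines, baseline-adjusted regression on the observed post scores carries the same information about the group effect as a likelihood fit. The simulation therefore shows that the check is uninformative in Part A and misleading in Part B. It does not measure the bias that the plan's rule would cause in this trial.

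**The case against.** The strongest reply has four parts.

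- **The article speaks of analyses, not a test.** They could be a review of missingness patterns and documented dropout reasons, used to judge whether MAR is plausible. Such a review is sensible and should be kept. But the next sentence still makes the method depend on its outcome, and no such review can establish MAR.

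- **The main model carries no such condition.** This stands. The missing-data sentence covers missing values in general and does not single out the primary outcome. If the mixed model is fitted by likelihood, the practical effect on the primary analysis is limited. It would overstate the point to say that the primary analysis hangs on the condition.

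- **The article states no fallback to completers.** A reader might infer that a negative result leaves a completers-only analysis, because nothing else is offered. The documents do not support that: the stated aim is to include as many patients as possible, and "the intention-to-treat analysis is preferred". The method for the other outcome could properly sit in a statistical analysis plan that is not shown. Nor does the word preferred show that the analysis set will be chosen once results are known. These are at most points of wording.

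- **A tempting illustration does not measure this fault.** Suppose 20% of the intervention arm leave and gain nothing, while completers gain 0.44 SD. The effect in all randomised patients is 0.8 × 0.44 = 0.352, and 0.44 / 0.352 = 1.25, so the completer figure is 25% too large. Both inputs are assumed. This is MNAR dropout: if nothing observed predicts who leaves, a mixed model under MAR would also return about 0.44. The figure supports a sensitivity analysis and says nothing about the cost of the condition.

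**Conclusion.** Wrong as written. The fault lies in a rule the article states, so it cannot be put down to detail left to another document. Maximum likelihood is tied to a finding that observed data cannot supply or, on the MCAR reading, to a finding it does not need. That conclusion is logical and does not rest on the simulated inputs.

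Its size in this trial cannot be given. The article states no dropout rate, and the effect depends on whether the named mixed model is fitted by likelihood. If it is, the rule is mainly an inconsistency that leaves an avoidable choice of method until after the data are seen. If it is not, patients with incomplete records could be lost from the primary comparison. The documents do not settle which applies.

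**What to change.** Delete the sentence that makes maximum likelihood conditional. In its place, state that the primary analysis is the likelihood-based (REML) mixed model in all randomised patients, by randomised arm, using all available visits, with MAR assumed in advance and whatever any missingness check shows. This also settles the intention-to-treat wording. Missingness patterns may still be described, but they should not decide the method.

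Add one MNAR sensitivity analysis, for example reference-based (intervention dropouts follow the waitlist trajectory) or delta-adjusted, informed by the dropout reasons the trial already records.

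The cost is two sentences and one extra run. The sample size, visits and intervention do not change.
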